# Efficiency of probiotics in elderly patients undergoing orthopedic surgery for postoperative cognitive dysfunction: a study protocol for a multicenter, randomized controlled trial

**DOI:** 10.1186/s13063-023-07167-6

**Published:** 2023-02-25

**Keywords:** Probiotics, Orthopedic surgery, Postoperative cognitive dysfunction, Randomized controlled trial

## Abstract

**Background:**

Postoperative cognitive dysfunction (POCD) refers to a neurological dysfunction after a major surgery and anesthesia. It is common in elderly patients and is characterized by impairment in consciousness, orientation, thinking, memory, and executive function after surgical anesthesia. However, at present, there is no definite preventive or treatable strategy for it. Previous animal experiments showed that giving probiotics to mice before operation can prevent POCD, but there is a lack of clinical evidence. This study aims to intervene with the intestinal flora imbalance using probiotics during the perioperative period to reduce the incidence of POCD in elderly patients after orthopedic surgery and to provide new ideas and methods for the clinical prevention and treatment of POCD.

**Methods:**

A multicenter, double-blind, placebo-controlled clinical trial will be performed to evaluate the efficacy of probiotics in elderly patients undergoing orthopedic surgery. Participants (*n* = 220) will receive probiotics (Peifeikang, Live Combined Bifidobacterium, 210 mg per capsule, twice a day, four capsules each time, which contains Bifidobacterium longum, Lactobacillus acidophilus and Streptococcus faecalis no less than 1.0 × 10^7^ CFU viable bacteria respectively) or placebo from 1 day before surgery to 6 days after surgery. Neuropsychological tests will be performed 1 day before surgery and 1 week and 1 month after surgery. The main outcome of this study is the incidence of POCD 7 days after surgery. Our secondary objective is to assess the incidence of POCD 1 month after surgery; the cognitive status will be determined based on a telephone interview and will be evaluated via TICS-m; postoperative delirium will be assessed 7 days after surgery using the Confusion Assessment Method (CAM).

**Discussion:**

Discovering the correlation between the intestinal microbiota and POCD is an important breakthrough. Based on the key role of the intestinal microbiota in other cognitive disorders, we hope that probiotics can reduce its incidence in elderly orthopedic patients.

**Trial registration:**

ClinicalTrials.gov NCT04017403. Registered on August 15, 2019.

**Supplementary Information:**

The online version contains supplementary material available at 10.1186/s13063-023-07167-6.

## Introduction

### Background and rationale

Postoperative cognitive dysfunction (POCD) refers to cognitive function changes, such as decreased learning and memory ability and inability to concentrate, after anesthesia and surgery. In severe cases, personality changes and decreased social behavior ability are observed [1]. Some patients even develop irreversible cognitive impairment [2]. POCD increases the hospitalization time of patients, prolongs their stay in intensive care units, increases their medical expenses, and increases the mortality of patients 1 year postoperatively [3]. POCD have become a widespread concern of clinicians and patients. Clinical studies showed that its incidence after a major surgery is relatively high, and major surgeries are often accompanied by blood redistribution caused by factors, such as bleeding and hypotension, resulting in intestinal mucosal ischemia [4, 5]. Intestinal mucosal ischemia is an important cause of intestinal flora imbalance [6, 7]. Patients with severe diseases (including sepsis, acute respiratory distress syndrome, and multiorgan failure) and those undergoing intestinal surgery are prone to changes in the intestinal flora. They are more likely to have intestinal flora disorders due to long-term applications of antibiotics, unstable hemodynamics, long-term parenteral nutrition, and other factors [8]. Such patients are more prone to POCD [9]. Its incidence in patients undergoing intestinal surgery is also relatively high. Tan et al. [10]. found that its incidence after an endoscopic or open colectomy is approximately 47%.

Studies in our laboratory proved that [11] giving probiotics to mice before operation can prevent POCD. However, at present, there is a lack of clinical evidence. In this study, probiotics will be used to intervene with the intestinal flora imbalance perioperatively in order to reduce the incidence of POCD and provide new ideas and methods for its clinical prevention and treatment.

## Methods

### Study design and setting

In this study, we will recruit 220 participants from Renji Hospital, School of Medicine, Shanghai Jiaotong University, Shanghai Guanghua Integrated Traditional Chinese and Western Medicine Hospital, and Shanxi Jincheng Hospital. The clinical trial was approved by the Ethics Committee of Renji Hospital (2018–232) and registered at ClinicalTrials.gov on August 15, 2019 (No. NCT04017403). The trial was conducted according to the recommendations of the Standard Protocol Items: Recommendations for Interventional Trials (SPIRIT) (supplemental file, SPIRIT checklist). We presented the trial registration data in the form of supplemental data.

This is a multicenter, double-blind, randomized, placebo-controlled, interventional superiority clinical study. We will observe the effect of perioperative probiotics on the postoperative cognitive function of elderly patients undergoing orthopedic surgery.

### Objectives

The purpose of this study is to determine whether the perioperative intervention with probiotics on intestinal flora can reduce the occurrence of POCD and to provide new ideas for its clinical prevention and treatment. Our primary objective is to assess the incidence of POCD 7 days after surgery. Our secondary objective is to assess the incidence of POCD and postoperative delirium (POD) 1 month and 7 days after surgery, respectively. We predict that probiotic intervention will reduce its incidence in elderly patients undergoing orthopedic surgery.

The schedule of the major study events for each visit is shown in Fig. 1. Patients who are scheduled to undergo orthopedic surgery will be included in this study. The entire process of recruitment and consenting of study participants by members of the research team will be consistent with good clinical practice (GCP) recommendations. Patients will be recruited mainly from the three centers.

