### Participant timeline

Figure 1 presents the schedule for enrollment, interventions, assessments, and visits of participants.

Cognitive function assessment: 1 day before operation: Mini-Mental State Examination (MMSE) screening, digit span test, digit symbol test, Wechsler Memory Scale (WMS), visual regeneration, and digital connection test will be performed. 7 days after operation or before discharge: digit span test, digit symbol test, WMS, visual regeneration, and digital connection tests will be performed again. 7 days after operation: POD will be assessed using the CAM, which includes acute onset, inattention, disorganized thinking, and abnormal consciousness. The diagnosis of delirium by CAM requires the presence of features 1 and 2 and either 3 or 4. Table 2 presents the specific content.

**Table 2 Tab2:** Specific content of the Confusion Assessment Method

The Confusion Assessment Method (CAM)	
Feature 1	Acute change in mental status with a fluctuating course Is there evidence of an acute change in mental status from the patient’s baseline? Did this behavior fluctuate during the past day, that is, tend to come and go or increase and decrease in severity? This feature is usually obtained from a family member or nurse and is shown by positive responses
Feature 2	Inattention Do the patients have difficulty focusing attention, for example, being easily distractible, or having difficulty keeping track of what was being said?
Feature 3	Disorganized thinking This feature is shown by a positive response to the following question: Was the patient’s thinking disorganized or incoherent, such as rambling or irrelevant conversation, unclear or illogical flow of ideas, or unpredictable switching from subject to subject?
Feature 4	Altered level of consciousness Overall, how would you rate this patient’s level of consciousness? (alert [normal], vigilant [hyperalert], lethargic [drowsy, easily aroused], stupor [difficult to arouse], or coma [unarousable])

The diagnosis of delirium by CAM requires the presence of features 1 and 2 and either 3 or 4

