We will also assess the long-term cognitive status using a modified cognitive state telephone interview (TICS-m) 1 month after surgery. TICS-m has been used to screen for dementia and mild cognitive impairment. The TICS-m score ranges from 0 to 48. The higher the score, the better the function. An evaluator will comprehensively evaluate the patient’s condition according to the patient’s medical history, clinical observation, current scale evaluation, and information provided by family members or nursing staff.

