Before surgery, the doctor will conduct medical visits for up to 40 min and complete the scale for each patient; furthermore, they will inform the patients that they will be followed up and observed for several consecutive days after surgery. If necessary, the doctor will communicate with the patient through WeChat to understand their latest situation in addition to communicating through phone calls. One day before surgery, the anesthesiologist will record each patient’s general information, including sex, years of education, BMI, dietary habits, history of disease, medication, and surgery. During surgery, blood pressure fluctuations are maintained within 20% of the baseline blood pressure level. Anesthesiologists will record the volume of infusion, estimated blood loss, and urine output and assess the need for a blood transfusion. Similarly, the duration of surgery, anesthesia, and hospital stay after surgery are recorded. After surgery, an analgesia pump will be used for intravenous self-analgesia (uniformly prepared by the pharmacy). Patient-controlled analgesia and or nerve block would be used for postoperative analgesia in all patients to maintain a VAS score of less than 3. The PCIA pump includes the following analgesics: sufentanil citrate 100 μg and flurbiprofen axetil 100 mg which are prepared into 0.9% sodium chloride, in a total volume of 100 ml. All patients receive a 1.5 ml on-demand bolus with a lockout interval of 15 min. The infusion was started immediately after suturing the skin incision and lasted 48 h. We use morphine as rescue drug, which is given according to the patient’s pain situation. At the same time, the drug dosage of the patient’s analgesia pump used and morphine dosage are recorded. Three months after operation, the same doctor will call the patient again for follow-up. All data collected during this clinical study will be entered and/or filed in the patients’ CRFs. The patients’ study participation must be documented appropriately in the CRF with their study number, subject number, date of subject information, informed consent, and date of each visit. Source data will be filed according to the GCP guidelines. The data manager will be responsible for data processing, following the sponsor’s standard operating procedures.

Regular monitoring will be conducted to ensure that the data are adequate, accurate, and complete. The database will be locked only after the completion of quality assurance procedures.

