### Outcome measures

#### Primary outcome measures

Our primary objective is to assess the incidence of POCD 7 days after surgery. The assessment of cognitive function was completed 1 day before operation and 7 days after operation or on the day of discharge by the following scales: digit span test, digit symbol test, Wechsler Memory Scale (WMS), visual regeneration, and digital connection test. The POCD was defined as follows:

The data of each patient consists of preoperative and postoperative data. The *Z*-score is used to determine whether the patient had POCD [13]. The positive result is at least one *Z*-score ≤ 2 (Wechsler word recall, visual reproduction, number symbols, number width) or ≥ 2 (number lines).

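### The 1-month secondary objective (incidence of POCD) does not match the 1-month outcome and test that the plan describes (a telephone TICS-m score compared by t-test)

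*Protocol article*

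**What the plan says.** All references are to the protocol article.

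- **Objectives:** "Our secondary objective is to assess the incidence of POCD and postoperative delirium (POD) 1 month and 7 days after surgery, respectively". So the 1-month item is a proportion of patients with POCD. The Abstract (Methods) names the same objective, follows it with a reference to TICS-m by telephone, and states: "Neuropsychological tests will be performed 1 day before surgery and 1 week and 1 month after surgery".
- **Primary outcome measures:** POCD rests on paired testing, "The data of each patient consists of preoperative and postoperative data", and on this rule: "The positive result is at least one *Z*-score ≤ 2 (Wechsler word recall, visual reproduction, number symbols, number width) or ≥ 2 (number lines". The assessment times given there are the day before operation and day 7 or discharge.
- **Participant timeline:** the preoperative list begins "1 day before operation: Mini-Mental State Examination (MMSE) screening, digit span test, digit symbol test, Wechsler Memory Scale (WMS), visual regeneration". The repeat is described as "7 days after operation or before discharge: digit span test, digit symbol test, WMS, visual regeneration, and digital connection tests will be performed again". For 1 month the text says: "We will also assess the long-term cognitive status using a modified cognitive state telephone interview (TICS-m) 1 month after surgery". TICS-m is described as a 0–48 score on which higher is better.
- **Secondary outcome measures:** two items are listed, delirium by CAM and cognitive status at 1 month by TICS-m. POCD at 1 month is not among them.
- **Statistical analysis:** the primary outcome is compared by chi-square or Fisher's exact test, and secondary outcomes by t-test.
- **Data collection and management:** "Three months after operation, the same doctor will call the patient again for follow-up".

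**The concern.** An objective should correspond to a listed outcome, a rule for deriving it and a test that suits it. Here the objective is an incidence, the listed outcome is a score, and the definition of the event belongs to other instruments at other times. As written, one of two things could happen. The stated objective could go unanswered, or a 1-month POCD rate could be produced by a rule chosen once the data are available. The Participant timeline leaves room for the second: it has an evaluator form an overall judgement from history, observation, scales and family or staff information, and gives no decision rule. A later reader could not tell whether a reported 1-month POCD rate was the planned quantity.

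**Working it through.** **The plan's own figure.** The article's only calculation is the sample size, and it concerns POCD at day 7. With p1 = 0.25, p2 = 0.10, two-sided alpha 0.05, power 0.80 and pooled variance (mean proportion 0.175):

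n = [1.960 × √(2 × 0.175 × 0.825) + 0.842 × √(0.25 × 0.75 + 0.10 × 0.90)]² / 0.15² = (1.053 + 0.443)² / 0.0225 ≈ 99.5, so 100 per group.

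This agrees with the stated 100. It does not bear on the 1-month outcome.

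**Can 1-month POCD incidence be derived from the text?**

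| Element | What 1-month POCD incidence needs | What the Methods describe |
|---|---|---|
| Instrument | The battery in the POCD rule | TICS-m by telephone |
| Timing | Battery preoperatively and at 1 month | Battery preoperatively and at day 7 or discharge |
| Rule | Z-score rule on the named tests | None linking TICS-m to POCD |
| Outcome list | A POCD item at 1 month | A cognitive status item by TICS-m |
| Test | Chi-square or Fisher | t-test |

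Every row differs. The last row is the weakest evidence of intent, because the t-test sentence covers all secondary outcomes, including delirium, which is also yes/no. The sign of the printed Z cut-off is a separate matter and is not relied on here.

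**The abstract's sentence on 1-month testing.** It can be read in two ways:

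1. It means the battery. Then POCD could be derived at 1 month, but the Participant timeline and Secondary outcome measures sections are wrong or incomplete.
2. It loosely means TICS-m. Then those sections stand, and the objective has no derivation.

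Neither reading makes the sections agree.

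**Precision of the TICS-m comparison.** Let r be the correlation of the 1-month TICS-m score with the baseline covariate (the multiple correlation if several are used). ANCOVA multiplies the variance of the treatment comparison by about 1 − r², which is equivalent to 1/(1 − r²) times as many patients. The documents give no value of r. For illustration only:

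- r = 0.5: 1 − 0.25 = 0.75; 1/0.75 = 1.33
- r = 0.7: 1 − 0.49 = 0.51; 1/0.51 = 1.96

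As r approaches 0 both factors approach 1. For MMSE, r is probably at the lower end, because patients scoring below 24 are excluded and the range is restricted.

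**The case against.** The best defence is that the outcome section is coherent by itself: a TICS-m score at 1 month, compared by t-test, needs no cut-off. On that view only the wording of the Abstract and Objectives is loose. The article also condenses a fuller protocol, its schedule figure is not shown, and a TICS-m threshold could sit in an analysis plan. Much of this stands. The missing threshold is not a finding in itself. What remains is that the article's own sections name different 1-month quantities, and an analysis plan would first have to choose between them.

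Four stronger readings are tempting, and the documents do not support them:

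- **That only TICS-m is taken at 1 month, with none of the POCD tests.** The abstract says otherwise, and the figure that might settle it cannot be seen. The same caution applies to the absence of a preoperative TICS-m, which rests on the text list alone.
- **That the follow-up call is at three months instead of one.** The sentence says the patient is called again, which points to an additional contact. The fault is only that no objective or outcome uses it.
- **That a TICS-m comparison without a preoperative TICS-m is biased.** With 1:1 randomisation, prior level balances in expectation. What is lost is precision, and any statement about decline within a patient.
- **That the loss equals 33% to 96% more patients.** Those figures come only from the illustrative correlations above and cannot be carried over to MMSE.

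**Conclusion.** The concern holds as an internal inconsistency in a secondary outcome. The article promises POCD incidence at 1 month, while its outcome list, event definition, schedule text and test describe something else. Confidence in the mismatch is high, because it rests on sections that can be read side by side. Which side is wrong cannot be decided without the schedule figure. The primary outcome and its sample size are unaffected.

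The consequence is an unclear secondary claim, not a quantifiable bias. The use of an unadjusted t-test is a smaller, separate point about efficiency. It assumes some correlation between baseline cognition and 1-month TICS-m, and its size cannot be stated from the documents.

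**What to change.** 1. **Align the objective with the measurement.** If TICS-m is the 1-month instrument, restate the objective in the Abstract and Objectives as the TICS-m score at 1 month and make no claim about POCD incidence then. Correct the abstract's sentence on neuropsychological tests to match. If a yes/no TICS-m outcome is also wanted, fix its rule before unblinding.
2. **Alternatively, if the battery really is repeated at 1 month,** say so in the Participant timeline and Secondary outcome measures, apply the POCD definition there, and compare groups by chi-square or Fisher's exact test. This suits only a battery that is already being given, since patients past 1 month cannot be tested retrospectively.
3. **Analyse 1-month TICS-m by ANCOVA** instead of an unadjusted t-test, with treatment and baseline cognition scheduled for all patients (battery scores, MMSE or both) and the covariates named in advance. No new data are needed.
4. **State the purpose of the 3-month call,** or say that it feeds no outcome.

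A preoperative TICS-m should not be added now. Recruitment began in December 2019 and was expected to end around December 2023, and the article appeared in February 2023. Only late enrolees would have the score, and combining it with MMSE for the others would put two scales into one covariate.

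The cost is a wording amendment, which by the article's own amendment rule needs ethics committee consent, and under option 1 the loss of one named objective.

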**Fig. 1 Fig1:**
[figure not shown]
The schedule of major study events that follows the Standard Protocol Items: Recommendations for Interventional Trials (SPIRIT) figure of enrolment, interventions, and assessments

### Eligibility criteria

The inclusion/exclusion criteria are summarized in Table 1.

**Table 1 Tab1:** Inclusion/exclusion criteria

Inclusion criteria	Exclusion criteria
1) Age is greater than or equal to 65 years old 2) Can communicate normally 3) Elective knee ankle, hip replacement, or lumbar open reduction and internal fixation under general anesthesia 4) ASA graded at I–II level 5) Patient or family informed consent	1) Have a brain disease, or have a history of brain disease 2) MMSE check of less than 24 points 3) History of neurological and psychological disorders including AD, stroke, psychosis 4) Serious hearing or visual impairment 5) Preoperative systolic blood pressure > 190 mmHg, or diastolic blood pressure > 100 mmHg 6) The patient or family refuses

### Consent

After assessing the patient’s eligibility for inclusion, his/her informed consent will be obtained. A designated doctor will explain the experiment in detail to interested participants and provide them with informed consent. Participants will have at least 24 h to decide whether they want to participate in the trial. An informed consent form will be signed by the participants or their trustee or guardian; it can be withdrawn at any time during the trial. A written informed consent and patient baseline data will be obtained before randomization. Moreover, participants will be encouraged to contact the research team if they have any health concerns during the trial.

We will collect baseline data from patients and randomize allocation using Statistical Analysis Set (SAS) software. Furthermore, participants can contact our team if they have any health concerns during the trial. The recruitment and consenting of study participants by the research team are in line with the GCP guidelines. During the clinical trial, the researchers will immediately report any serious adverse events, whether related to the probiotics under study or not, to the director in charge of the clinical trial of the research institution and contact [name] or [name].

No ancillary study is planned, and we have no plans to collect additional participant data or biological specimens outside of what is mentioned in this protocol.

Participant information will be confidential and managed according to the Data Protection Act, NHS Caldecott Principles, The Research Governance Framework for Health and Social Care, and the conditions of Research Ethics Committee approval.

